## Abstract

**Background:**

Medical treatment in patient-centred care in oncology is broadly managed and regulated in terms of guideline development, cancer centres, and quality assurance by cancer registries. In contrast to this quality management cycle (PDCA), there are no equal standards for patient-reported outcomes like quality of life (QoL). Therefore, the Tumour Centre Regensburg e.V., a population-based regional cancer registry covering a population of more than 2.2 million people in the Upper Palatinate and Lower Bavaria, Germany, designed and implemented a QoL pathway. In a complex intervention with QoL diagnosis and therapy (multidimensional therapeutic network), effectiveness for patients with breast cancer has been demonstrated. To provide local tailored QoL diagnosis and therapy to other cancer patients as well, external validity needs to be extended by adapting the QoL pathway to another tumour entity.

**Methods/Design:**

The QoL pathway will be tested for colorectal cancer patients in a pragmatic randomised controlled trial. Two hundred twenty primary colorectal cancer patients, surgically treated in one of four hospitals, will be included. QoL is measured in all patients 0, 3, 6, 12, and 18 months after surgery (European Organisation for Research and Treatment of Cancer (EORTC) QLQ-C30, QLQ-CR29). In the intervention group, QoL scores are transformed into a QoL profile. This is sent to the coordinating practitioner (general practitioner, internist, or oncologist) with an expert report including treatment recommendations for QoL deficits. The control group receives routine follow-up care attending the guideline recommendations for colorectal cancer without profile or expert report. At the primary endpoint (12 months), the rates of patients with diseased QoL in both groups are compared.

**Discussion:**

This randomised trial is the first complex intervention investigating the effectiveness of an intervention with QoL diagnosis and tailored QoL therapy in colorectal cancer patients. The results will show if this QoL pathway improves the patients’ QoL during follow-up care of their disease.

**Trial registration:**

ClinicalTrials.gov, NCT02321813 (registered December 2014).

## Background

There is a growing interest in using quality of life (QoL) data not only as a relevant endpoint in clinical trials on cancer patients, but also in routine practice in order to improve patients’ health during treatment [1–4].

Until now, several essentials for managing ‘diseased QoL’ have been missing. First of all, there is a need of guidance about how to define and use diseased QoL as an integral part of cancer treatment, for example, in patients with good prognostic stage (UICC 0 and I) but persistently low QoL in several dimensions requiring the doctor’s help [5]. Furthermore, therapies rarely have been implemented specifically to improve patients’ QoL. Additionally, there needs to be confidence in the evidenced-based value of such QoL therapies [6].

To achieve these aims, we designed, implemented, and evaluated an integrated QoL diagnosis and therapy pathway (QoL pathway) for breast cancer patients, guided by the UK Medical Research Council framework for developing and testing complex interventions [7]. In a previous randomised controlled trial it could be demonstrated in a routine setting that breast cancer patients show a benefit from tailored QoL diagnosis and therapy, having significantly better QoL 6 months after surgery compared to a control group treated with routine follow-up care [6].

In order to extend the external validity of our approach it is necessary to apply its principles to another tumour entity. Colorectal cancer was chosen for the following reasons: It is the second most common form of cancer in the Western world (69,000 new diagnosed patients/year in Germany), responsible for about 27,000 cases of death per year in Germany [8]. The demands of this cancer form on QoL diagnosis and therapy differ in some important aspects from those in breast cancer (for example, more important part of surgical procedure because of the more extended severe tumour extirpation and patients of both sexes, with higher age and more comorbidities).

Many studies have demonstrated that various components of the QoL of colorectal cancer patients are considerably impaired. QoL deficits are most dominant during the first months after surgery with some discomfort persisting for a longer time, for example, impaired body image or sexual problems [9]. One year after diagnosis, colorectal cancer patients still suffer fatigue and reduced emotional functioning compared to the general population [10]. Special aspects concerning this form of cancer are stoma-related complications. The presence of a stoma is associated with more psychological distress and reduced sexual functioning [11] while stoma reversal leads to a significant improvement in physical and social functioning and overall QoL [12]. Furthermore, it was shown that baseline QoL is a significant prognostic indicator for survival in advanced colorectal cancer, with better QoL being associated with a higher 1-year survival rate [13].

There is general agreement that QoL needs to be not only considered as an endpoint in clinical trials but also in routine health care of cancer patients. The mainstream of research has focused on developing a routine measurement of QoL in clinical practice and providing the results to clinicians in order to improve patient-physician communication [1, 2, 14, 15]. These studies, however, provide no clues how to deal with this information because specific implications for the treatment of QoL deficits never have been spelled out.

Therefore, we developed a QoL pathway, which connects a systematic QoL diagnosis with targeted treatment of QoL deficits in breast cancer patients. Because of the complexity of the healthcare system, the study was conducted as a complex intervention [7, 16] with theory building [17, 18], modelling [5], exploratory trial [19], and a definitive randomised controlled trial [6]. In the present randomised trial, effectiveness of the QoL pathway, modified for colorectal cancer patients, is to be tested.

### Objectives and hypothesis

The primary objective of the study is to improve QoL of colorectal cancer patients during follow-up care with systematic QoL diagnosis and targeted treatment. To achieve this aim, the following key issues are addressed:Testing effectiveness of the QoL pathway with systematic diagnosis and targeted therapy of QoL in colorectal cancer patients during follow-up care.Implementing the QoL system into routine medical care using a multifaceted strategy including educational outreach visits, local opinion leaders, and continuous medical education (CME) (in defined and modelled quality circles [5]).Extension of regional network structures for QoL therapies by creating new quality circles and by expanding the already existing quality circles.Extension of external validity by applying the QoL pathway in another tumour entity.Replication of the findings as an essential part of complex interventions.

The following hypothesis will be investigated:

Colorectal cancer patients who receive systematic QoL diagnosis and targeted QoL therapy (intervention) have a significantly better QoL in the first postoperative year compared to patients who receive routine follow-up care (control).

## Methods/Design

The study is a two-armed, randomised, controlled, prospective, single-blind, pragmatic, clinical trial with an intervention group and a control group.

### Participants and recruitment

Four hospitals with certified colorectal cancer centres in Bavaria, Germany, accredited by the German Cancer Society (DKG), take part in patient recruitment: Krankenhaus Barmherzige Brüder, Department of Surgery, Regensburg; Caritas-Krankenhaus St. Josef, Department of Surgery, Regensburg; Klinikum Neumarkt, Department of Surgery, Neumarkt; Klinikum St. Elisabeth Straubing, Department of Surgery, Straubing. Before the beginning of the trial the number of patients fulfilling the inclusion criteria has been collected in the four hospitals for the year 2011 in order to see if enough eligible patients are available. There has been a pilot phase in the hospitals for the QoL pathway in order to implement patient recruitment and postsurgical QoL measurement into clinical routine. To achieve an adequate participant enrolment there is regular contact between the QoL Unit and the surgeons recruiting patients in the four hospitals. Moreover, the participating clinics are certified cancer centres that need enrolment of patients into studies for the certification process and thus should be highly motivated to include patients in the trial.

Patients are included under broad inclusion criteria: (1) diagnosis of primary colorectal cancer and (2) surgery in one of the four participating hospitals. Exclusion criteria are as follows: (1) recruiting surgeon (QoL clinician) is not available (illness, holiday, other reasons); (2) patient is misclassified in the operation schedule (no primary operation or no colorectal tumour); (3) coordinating practitioner (physician, caring for the patient) chosen by the patient refuses trial participation; (4) patient is from outside the defined study region (Bavaria, Germany: urban county of Regensburg, rural county of Neumarkt, Straubing, Straubing-Bogen, Kelheim, Schwandorf); (5) age under 18 years; (6) pregnancy; (7) patient unable to fill out the QoL questionnaire for physical, psychological, or language reasons (including dementia); or (8) patient refuses to participate in the study. To insure high external validity [20] , there will be no exclusion of elderly patients or exclusion according to tumour stage or patient sex. Furthermore, no constraints will be made according to surgical procedure or ASA score (American Society of Anesthesiologists); however, these factors will be accounted for in data analyses. External validity is also kept high by population-based inclusion of patients of urban and rural areas and by implementing the QoL pathway into routine follow-up care. Moreover, data of the cancer registry of excluded patients and other hospitals in the study region can be analysed according to medical and demographic data of patients to test representativeness of our study population. The selection of study participants is shown in Fig. 1.

**Fig. 1 Fig1:**
[figure not shown]
Selection of patients

Coordinating practitioners (CPs) are defined as those physicians who care for the colorectal cancer patients after hospital stay. They are either general practitioners, or internists, or oncologists. CPs are eligible for the project if they give their informed consent to participate in the trial (CP is informed by the patient’s surgeon by phone about the study) and agree to be implemented by an educational outreach visit. Outreach visits are performed by two trained individuals of the QoL Unit who meet with the CP in his practice and introduce him to the concept of QoL, stressing the importance of considering QoL in medical care of colorectal cancer patients and who give the CP an overview about the procedure of the study. Outreach visits are structured by using fixed presentation slides for the implementation of each CP.

### Randomisation and blinding

Balanced randomisation [21] is used with random permuted blocks of 20 patients followed by a sequence of 11 blocks for 220 patients with a second, simple randomisation. Five digit random numbers from the RAND Corporation [22] are used for both steps. Based on this random list of digits an external co-worker, otherwise not involved in the trial, created 220 paper cards specifying the groups and inserted them in 1 to 220 serially numbered opaque, sealed envelopes. This stack of envelopes is kept in a locked safe at the QoL Unit at the Tumour Centre Regensburg and is accessible only by the two study coordinators.

Randomisation of individual patients is performed using the following described procedure. The study clinician in each of the four recruiting hospitals determines eligibility of the study patient. If all criteria are fulfilled and the patient has granted informed consent the study clinician sends the recruitment document to the QoL Unit. The study number 1 to 220 is determined by the exact date and time of fax entry. The CP will be informed by the QoL Unit about allocation of the individual patient either to the intervention or the control group.

The CP will be obliged not to share this knowledge with the patient. In order to control for bias, participants will be kept blind throughout the study about their allocated group (single blind design). At the end of the trial, the patients’ blindness about their allocated group will be checked.

At no point in the process will the recruiting clinician in the hospital access the sealed envelopes or be informed about the group allocation.

### Procedure

Written informed consent is obtained from each participant before they are included into the study. All participants (intervention and control group) repeatedly fill out a QoL questionnaire (EORTC QLQ-C30, QLQ-CR29 [23–25]) at the following times: 0 to 2 days before discharge from hospital and 3, 6, 12 and 18 months postoperatively. The first QoL measurement takes place in hospital and the further measurements (3, 6, 12, 18 months postoperatively) are carried out in the CP’s practice during follow-up. For each assessment time point participants receive a postal reminder. Guideline for colorectal cancer [26] recommends first follow-up at 6 months. Colorectal cancer patients suffer a lot of QoL deficits especially in the first months of treatment. Therefore, we decided also to measure QoL 3 months postoperatively. Feasibility of this additional measurement is expected to be good because most patients visit their CP regularly. This could be also observed in the pilot phase of the study.

Parallel to the QoL measurements, the patient’s CP provides additional information about the patient’s health status. All data are sent to the QoL Unit at the Tumour Centre Regensburg.

All patients are treated according to the follow-up regimen of S3-guideline for colorectal cancer [26]. Concomitant care is not prohibited but will be collected and considered in secondary data analysis.

Differences between the treatment of intervention group and control group patients is shown in the following section. Figure 2 gives an overview of the study flow in the two arms of the randomised trial.

**Fig. 2 Fig2:**
[figure not shown]
Trial profile: patients flow through each stage in two arms of the randomised controlled trial (CP, coordinating practitioner)

#### Intervention group

The QoL pathway for intervention group patients is shown in Fig. 3. All intervention group patients receive, in addition to routine follow-up care [26], tailored QoL diagnosis and therapy during the first 18 months after surgery. For this purpose measurements of a QoL questionnaire (EORTC QLQ-C30, QLQ-CR29 [23-25]) are transformed into a QoL profile using a computerised visualisation programme [27]. The profile consists of scales of 0 to 100 (worst to optimal QoL) comprising global QoL and 12 different dimensions considering somatic (e.g. pain), psychological (e.g. emotional functioning), and social aspects (e.g. family life) (Fig. 4). The QoL profile also takes into account the specific discomfort colorectal cancer patients suffer, for example, disability during defecation, increased bowel movement, or discomfort during urination (EORTC QLQ-CR29). A cut-off score has been constructed, which defines scores < 50 points as ‘diseased QoL’.

**Fig. 3 Fig3:**
[figure not shown]
Patients in the intervention group (quality of life (QoL) pathway) following recruitment for the randomised trial. This pathway is considered for clinical routine

**Fig. 5 Fig5:**
[figure not shown]
Traditional and hermeneutic therapeutic options for patients with colorectal cancer. An integrated model

QoL of patients will be rechecked at 3, 6, 12, and 18 months postoperatively during follow-up in the practice of the CP with QoL diagnosis and therapy following the same procedure as described above.

#### Control group

In the control group patients’ QoL is also assessed before clinical discharge and at 3, 6, 12, and 18 months postoperatively during medical follow-up. In contrast to the intervention group, the CP of a control group patient is *not* informed about the results of patient’s QoL measurement (neither the QoL profile nor expert report are sent to him). Patients receive standard follow-up care according to the S3-guideline for colorectal cancer [26] (see Fig. 2).

### Measures

#### Quality of life (patient)

Quality of life is measured by using the validated QoL questionnaire of the European Organisation for Research and Treatment of Cancer (EORTC), consisting of a core module (EORTC QLQ-C30 [25, 28]) and a module for colorectal cancer patients (EORTC QLQ-CR29 [23, 24]). The questionnaire is a self-administration instrument with a multidimensional structure measuring QoL on a four-point Likert scale or rather on a seven-point Likert scale for the global dimension QoL. Satisfying internal consistency and good retest-reliability, as well as construct and clinical validity, have been demonstrated [24, 28, 29].

In every dimension scores are uniformly transferred to a scale from 0 (very bad QoL) to 100 (very good QoL). A cut-off score has been constructed, which defines scores < 50 points as diseased QoL. This score has been extensively discussed and accepted in the present form by consensus of a large group of clinicians [5, 6, 18].

For outcome measurement of the present randomised trial, 13 different scales have been selected according to the results of the previous randomised trial in breast cancer patients [6], the appraisal of relevance for QoL of colorectal cancer patients, and the availability of therapy options (global QoL, physical functioning, role functioning, pain, discomfort during defecation, increased bowel movement, discomfort during urination, body image, emotion, concentration/remembering, fatigue, family life/social encounters, and financial situation).

#### Health status (surgeon/CP)

The first measurement of health status is performed before discharge from the hospital. The surgeon gives information about the following demographic and medical characteristics of the patient: age, sex, marital status, children, occupation, ASA classification, tumour stage, date of surgery, surgical procedure, complications, comorbidities, (neo)adjuvant therapies, other current or planned therapies (for example, pain therapy, psychotherapy physiotherapy), CEA, preoperative symptoms, height, and weight. The type of surgery and ASA classification especially are expected to affect strongly colorectal cancer patients’ QoL [30]. These variables will be considered in data analysis, but neither specific surgical procedures nor higher ASA classifications will be excluded in order to achieve high external validity.

During follow-up the CP gives written information about health status at 3, 6, 12 and 18 months postoperatively regarding CEA, finished, current, or planned therapies, and complications. Additionally, the CP makes an assessment of the patient’s global QoL on a seven-point Likert scale.

#### Telephonic enquiries (CP)

Four weeks after the patient has filled out the QoL questionnaire, a member of the QoL Unit calls the CP by telephone and asks if anything has been done to improve the patient’s QoL. The reason for this is that in the intervention group CPs receive a QoL profile and an expert report with recommendations for improving their patients’ QoL. Therefore, whether anything has been done in response to the expert report is to be recorded by phone call. In order to ensure comparability of patients in both study arms, there are also telephonic enquiries for CPs of control group patients.

#### Patient satisfaction (patient)

After the patient has finished the last QoL measurement at 18 months postoperatively, a questionnaire will be sent to the patient’s home. The questionnaire includes quantitative and qualitative questions on patient satisfaction regarding (medical) care since the diagnosis of colorectal cancer and usefulness of the repeated QoL measurements. Additionally, the blindness of patients about their allocated group is checked.

### Ethics and monitoring

This study has received full ethical approval through the ethics committee of the University of Regensburg (internal reference number 12-101-0014). The trial is registered with ClinicalTrials.gov, trial registration number NCT02321813.

A central ethical question has to be answered before conducting a randomised trial: Is a new treatment denied to the control group from which those might benefit? In our study, control group patients are treated according to the S3-guideline for colorectal cancer (26) but do not receive additional targeted QoL therapy based on systematic diagnosis. Nevertheless, it can be expected that control group patients also benefit from study participation because their CP will also be trained in assessing QoL and therefore is expected to be sensitised for QoL deficits of his patient. It must also be considered that the new intervention or specific treatment of QoL might bear a risk for patients in the intervention group. Furthermore, emotional drain by filling out QoL questionnaires is conceivable. An insurance for patients’ safety was taken out to cover any possible harm of trial participants.

The randomised trial on breast cancer patients [6] did not show any evidence of possible harm elicited by the QoL pathway. For monitoring patient safety, patient’s CP is repeatedly contacted by phone about 1 month after the patient has filled out the QoL questionnaire (telephonic enquiries) and is asked whether he has recognised any negative effect on the patient. Serious adverse events, including death or admission to hospital, will be recorded, analysed, and reported to the local ethics committee.

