### Sample size

The trial sample size was calculated by means of the first primary endpoint (lack of a QoL deficit in the QoL profile, that is, all scores are ≥ 50 score points). Based on the randomised controlled trial on breast cancer patients (6), we expect that 45 % of the patients in the intervention group report no QoL deficit 12 months after therapy, but only 25 % in the control group. Setting α at 5 % and power (1-β) at 80 %, 89 patients are needed in each group in order to detect the hypothesised difference when calculating the *Χ*^2^ test. To compensate for 20 % drop-outs (death or refusal) within the 12 months observation period, we will enrol 110 patients per group, and thus, the total sample size will be 220.

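### The only active safety contact described is timed from a completed questionnaire, so patients who stop completing have no further safety call due and ascertainment of harm may be incomplete

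*Protocol article*

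**What the plan says.** Two sections of the protocol article describe the call to the CP. Under Telephonic enquiries (CP): "Four weeks after the patient has filled out the QoL questionnaire, a member of the QoL Unit calls the CP by telephone". Its stated purpose there is to learn whether anything was done in response to the QoL profile and expert report; CPs of control patients are called as well, for comparability. Under Ethics and monitoring the same call becomes the safety procedure: the "patient’s CP is repeatedly contacted by phone about 1 month after the patient has filled out the QoL questionnaire", and the CP "is asked whether he has recognised any negative effect on the patient".

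The next sentence of Ethics and monitoring adds a general commitment: "Serious adverse events, including death or admission to hospital, will be recorded, analysed, and reported to the local ethics committee". It names no source or reporting route.

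There is also a written report. Under Health status (surgeon/CP): "During follow-up the CP gives written information about health status at 3, 6, 12 and 18 months postoperatively". Its listed follow-up content is CEA, therapies, complications and the CP's own rating of global QoL. The Procedure section ties it to the assessments: "Parallel to the QoL measurements, the patient’s CP provides additional information about the patient’s health status".

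The Sample size section expects losses: "To compensate for 20 % drop-outs (death or refusal) within the 12 months observation period", which takes enrolment to 110 per group and 220 in total.

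**The concern.** Completion of a questionnaire is a sensible trigger for asking whether the CP acted on the resulting report. It is a poor trigger for safety, because patients who become seriously ill, refuse or die are the ones who stop producing questionnaires. The eligibility criteria set no upper age limit and no limit on tumour stage or ASA score, so serious illness during follow-up is foreseeable. Ethics and monitoring itself allows that the intervention may carry a risk and that filling out questionnaires may be an emotional burden. A patient who stops for that reason leaves the call schedule.

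At stake is the safety summary. If negative effects and admissions are actively sought mainly in patients well enough to keep answering, a finding of no harm could partly reflect the trigger. If the reasons for stopping differ between arms, so could ascertainment. The CP also knows the allocation (Randomisation and blinding), so events volunteered without a standard enquiry need not be reported equally in both arms.

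**Working it through.** **The plan's own figure.** Inputs from the Sample size section: 45 % against 25 % without a QoL deficit, α = 5 % (taken as two-sided), power 80 %, χ² test.

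n per group = [1.960 × √(2 × 0.35 × 0.65) + 0.842 × √(0.45 × 0.55 + 0.25 × 0.75)]² / 0.20² = [1.322 + 0.555]² / 0.04 ≈ 88.1, rounded up to 89.

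This matches the stated 89. The present point does not depend on it; what is used below is the enrolment of 220 and the 20 % allowance.

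**Patients with no 12-month call due.**

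- At the planned 20 %: 0.20 × 110 = 22 per group, 0.20 × 220 = 44 in total.
- If drop-out were 10 % (assumption): 0.10 × 220 = 22.
- If drop-out were 30 % (assumption): 0.30 × 220 = 66.

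These patients have no 12-month questionnaire, so a call timed from it never falls due. The article gives no split between death and refusal and no drop-out figure for months 12 to 18, so the count cannot be refined or extended to 18 months.

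**Routes by which harm could become known, side by side.**

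| Route | Timing as written | Asks about | Stated to continue after a patient stops completing? |
|---|---|---|---|
| Telephone call (Telephonic enquiries; Ethics and monitoring) | About 4 weeks or 1 month after completion | Actions taken; any negative effect | No: the trigger is completion |
| Written CP report (Health status; Procedure) | 3, 6, 12, 18 months, parallel to the QoL measurements | CEA, therapies, complications, CP's QoL rating; death and admission not listed | Not stated |
| Serious adverse event commitment (Ethics and monitoring) | None given | Serious events, including death and admission | Not stated; not made conditional either |

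Only the first route is an active enquiry about harm, and it is the one whose wording depends on completion. The article uses fixed postoperative dates for the assessments and the written report, so fixed dates were available for the call too. For patients who keep completing, an admission between assessments can still surface at the next call. The gap concerns those who stop.

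**The case against.** The strongest reply is that the article does not make serious event recording conditional on anything. The commitment to record deaths and admissions stands in its own sentence, and the written CP report falls at fixed dates after surgery and includes complications. The phrase linking that report to the QoL measurements is most naturally read as describing timing, not as making the report depend on the patient's response. A condensed article may also leave reporting routes and the handling of non-completers to the full protocol. Finally, a call four weeks after a questionnaire suits the intervention: without a new questionnaire there is no new expert report whose effects need checking.

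Much of this stands. A reader might infer that serious events in these patients are missed, or might take the share of follow-up time outside the four-week windows as the share of deaths missed. The documents support neither. Both readings require the call to be the sole route, and the article does not say that it is. Nor are the 44 patients 44 events: they include refusers with no known event, some of whom may withdraw consent to data collection.

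The reply does not remove the point. The trigger is not a missing detail; it is stated in two sections. The commitment to record events names no route, and neither it nor the written report is said to continue for patients who no longer complete. The rationale about the expert report explains the call's first purpose but not its reuse for general safety monitoring in both arms.

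**Conclusion.** The point holds as a weakness in a stated rule. The only active safety contact described is conditional on questionnaire completion, so read literally up to about 44 of 220 patients have no 12-month safety call due (22 to 66 for assumed drop-out of 10 % to 30 %). Ascertainment of negative effects and admissions may therefore be incomplete.

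It could differ by arm, but that is a possibility only: the documents give no evidence that refusal or illness would differ between groups. The conclusion rests on reading the trigger literally and on the plan's own drop-out allowance; the number of events affected cannot be derived from the documents. The primary endpoints and the sample size are untouched. This is a cheap improvement to safety ascertainment, not a flaw in the efficacy design.

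**What to change.** In Telephonic enquiries (CP) and in Ethics and monitoring, schedule the call about 1 month after each planned assessment date counted from surgery (the assessment before discharge and those at 3, 6, 12 and 18 months). Make it for every randomised patient in both arms, whether or not the questionnaire was completed, unless consent to data collection is withdrawn. At each call ask the CP about death and hospital admission since the last contact, in addition to the present question on negative effects. State that serious events are analysed in all randomised patients. The question about actions taken on the expert report can stay limited to patients who completed a questionnaire.

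For patients who complete on schedule the call falls at about the same time as now. The cost is a few extra calls by QoL Unit staff who already telephone CPs in both arms: at the 12-month assessment, up to about 44 at the planned drop-out rate. The sample size, the endpoints and the testing order do not change.
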